**2. Background to the study, including both policy relevance and related research**

*Ambulance service context*: Against a background of relentlessly increasing demand for emergency care1, growing knowledge that a substantial proportion of 999 callers do not need care at an A&E department2, and recent confirmation from the Department of Health that local responses should be developed for less serious calls, ambulance services are now exploring different ways of responding to callers across the spectrum of need. This has been reinforced by both the Reforming Emergency Care 3 agenda and the recently launched Department of Health ‘Taking Healthcare to the Patient: Transforming NHS Ambulance Services’4. Some services now have a policy of ‘No-send’ in some circumstances, many are testing the provision of further assessment and advice in place of the automatic dispatch of an ambulance, and a variety of responses are being trialled in the field including single manned cars and Emergency Care Practitioners (ECPs).

*Research evidence:* Unfortunately, the clinical, cost-effectiveness and safety of these initiatives are unknown, with these developments underpinned by little research evidence. In the face of very rapid service developments, formal evaluation has been an exception rather than the rule, despite the high risks associated with this area of NHS work. The proposed study builds on previous primary and secondary research carried out by team members, including:

1) Evaluation of telephone advice using computerised decision support software in ambulance control (TAS study)5

2) Evaluation of Treat and Refer protocols allowing crews to make decisions to leave patients at scene (T&R study)6

3) Evaluation of on-scene triage of older people who have fallen to transportation/home care (Fit to be Left study)7

4) Profiling of older fallers in South Wales 8

5) Evaluation of a paramedic practitioner service for older people in Sheffield (PPOPS)9

These studies have focused on the development and evaluation of provision of alternative services for 999 callers who do not clinically need to attend A&E. Each study has found that a large proportion of these calls are made up of older people who fall and for whom a 999 call is made. It is known that currently up to 10% of the 999 workload is made up of older people who have fallen (approximately 50,000 per year in London), with 40% of these calls resulting in attendance but non-conveyance – despite ambulance crews having no training nor formal protocols to make decisions to leave patients at scene. For older people who have fallen, telephone assessment and advice is usually of little benefit, but results from initial trials of on-scene triage and care planning have been encouraging 6,7,9. Although introduction of protocols allowing paramedics and emergency medical technicians to leave patients at the scene has been found to be feasible, their impact was limited by factors related to: cultural setting; insufficient training and support for new models of care; practical issues in implementation (reluctance to refer to paper based protocols in a face-to-face assessment); and problems in working across provider boundaries (weaknesses in systems of referral)10. Safety concerns have been raised also – related to both current practice, and practice following the introduction of protocols. This has reinforced some concerns highlighted by several studies in the USA focusing on triage abilities of paramedics for home care11-13. Early results of an evaluation of paramedic practitioners targeted to 999 calls for older people suggest, however, that a significant reduction in hospital admissions can be achieved9, although results concerning the safety of the service are not yet available.

*Falls:* With a growing population of older people, falls and their consequences are increasingly recognised as a priority area for clinical care, service delivery development and research. The consequences of falls in the over 65s are now well known in terms of mortality, disability, loss of independence and quality of life, as well as burden and cost for the NHS 3. Older fallers presenting at A&E have been shown to benefit from referral for inter-disciplinary assessment, although it is not known if these results would apply to the 999 group4. The National Service Framework for Older People specified that those who fall and for whom a 999 call is made should be referred to a Falls Team. However, achievement of this target is impeded by a lack of skills within the ambulance service to reliably assess older people’s needs and safely make decisions to leave patients at home, as well as a lack of referral systems for the onward care of older people who have fallen.

*Information Technology and the NHS*

Within the NHS there has been increasing recognition of the major role that information technology can play in healthcare. Strategic documents have highlighted the growing need to support patients and staff in the delivery and management of services 14-16. This research will contribute to the agenda of ‘informing health care’ by testing an innovative application of an IT based solution to a complex service delivery setting, testing whether IT can help to deliver ‘faster, safer and more convenient patient care’16.

*Application of technology in the emergency care of older people who fall*

In this study, clinical decision software (CDS), based on the system that has successfully been used in previous research with ambulance and out of hours services and modified through the T&R6 and Fit to be Left7 studies, will be used on-scene through a hand-held device to support paramedics to make triage decisions for older people who have fallen, in order to decide who should be taken to A&E and who can be left at home with self-care advice and/or onward referral to a community based service. The CDS has been developed in the UK to support nurses and paramedics to assess the clinical and social needs of patients presenting with acute problems in primary or emergency care. It is already being used by some ambulance services (e.g. Lincolnshire), out of hours services (e.g. Nottingham Emergency Medical Services) and NHS walk-in services (e.g. Gateshead). The CDS guides the user through all aspects of history-taking, examination and care planning, including referral and advice giving, and can be operated on a Tablet PC, making it ideal for use by ambulance service paramedics.

Although ambulance crews are generally receptive to using new equipment, having been trained to use increasing numbers of medical devices such as defibrillators and pulse oximeters in recent years, the acceptability of an IT based system for supporting their decision making on scene is unknown. Compliance with protocols for research, documentation and even treatment has been found to be weak in several studies 3,4,17. Hence a participative approach will be taken with crews and managers from the outset in order to ensure that the practical details of the development and implementation of the intervention maximise the chance of uptake and success in this evaluation.

**3. Purpose of the research**

The study addresses an important area of care – of older people who fall and require emergency aid. It combines a technological innovation with a new model of service delivery across provider boundaries. Evaluation of the costs and benefits of the technology in this complex setting will provide valuable information concerning the development of more appropriate care pathways, including linking with falls prevention strategies; and potential avoidance of hospital admissions for this vulnerable patient group.

**Study aim**: To assess costs and benefits of hand-held computerised CDS technology for the on-scene assessment and care of older people who fall and call the emergency ambulance service

**Objectives:**

**Primary objective:**

To compare between intervention and control group patients at one month and six months:

1) the number of further falls for which a 999 call is made, the time to the first of any subsequent falls; and the number of A&E attendances and hospital admissions

2) quality of life of patients and carers as well as their independence and satisfaction

3) operational ‘process’ indicators: on-scene times, job cycle times – from 999 call to ‘ambulance free’ time

4) impact on resource utilisation within the NHS and costs to patients and their families

and at each participating site, to explore

- implementation issues with service providers

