*Sample size*: The sample size for the two paramedic sites (S Wales and Great Western) is calculated for the primary objective, and with 20 paramedics (ten in each intervention group, 10 in each control group) at each site. Based on ambulance service data from the participating services, it is expected to recruit 250 older people who have fallen in each site each month. However, it may not be possible to identify all those who have fallen as eligible for inclusion in the study from information given during the 999 call, and some patients will not consent to be included. Using a conservative estimate of the recruitment of 80 older people who have fallen attended by study paramedics per month, a period of nine months will allow inclusion of 720 patients per site (1440 in total). With the 20 clusters, this will give more than 80% power at the 5% significance level to detect a drop in further 999 calls for falls from 50% (as found in London recently6) to 40%, assuming an intra-class correlation of less than 0.02, and to detect an effect size of 0.20 (i.e. one fifth of the population standard deviation) in SF12 scores.

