**Plans for data analysis**

Measures of process, outcome and cost will be compared between intervention and control groups patients according to ‘intention to treat’. As we expect a high rate of subsequent 999 calls for falls, it is likely that people may be attended for a fall on more than one occasion during the study period. Although, if the intervention is effective, the impact on outcomes may potentially be diluted by subsequent attendance by a paramedic or ECP using the computerised CDS, individuals will remain, for the purpose of the primary analysis, in the group to which they are first allocated. Time interval to first subsequent fall will also be compared between the two groups. Design and methods will comply with the standards laid down in the CONSORT guidelines21. Qualitative data will be analysed thematically using a content analysis approach.

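### The protocol names no single primary outcome or time point, and its stated power belongs to an undated proportion that the primary objective does not list

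*Protocol*

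**What the plan says.** Under Objectives, one objective is labelled primary: "To compare between intervention and control group patients at one month and six months". Its four numbered items cover:

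1. "the number of further falls for which a 999 call is made, the time to the first of any subsequent falls", plus A&E attendances and hospital admissions;
2. "quality of life of patients and carers as well as their independence and satisfaction";
3. "on-scene times, job cycle times";
4. "impact on resource utilisation within the NHS and costs to patients and their families".

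The Sample size paragraph says its calculation is for the primary objective. It claims power above 80% at the 5% level, with an ICC below 0.02 and 1440 patients, "to detect a drop in further 999 calls for falls from 50% (as found in London recently6) to 40" per cent, and also for an SF12 difference of 0.20 SD. Neither target carries a time point.

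The Description of intervention section says more broadly that the study will be powered for differences in both processes and outcomes at the two sites.

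Plans for data analysis mentions a primary analysis once, to fix the group in which a patient is counted. It names no outcome or time point. The Outcomes paragraph tracks service contacts for six months, collects SF12 at one and six months, and measures satisfaction at one month only.

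**The concern.** A trial is judged by its primary outcome. Here that label covers clinical events, quality of life, process times and costs at two time points, so the deciding result could be picked once the data are known, and nothing limits the overall error rate.

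The sample size does not settle the choice. It uses a percentage with a further 999 call, whereas item 1 names a number of falls and a time to event. The percentage is also undated, so a reader cannot tell whether the claimed power applies at one month or at six. Finally, the general statement about processes and outcomes goes beyond the calculation: nothing is computed for process times, A&E attendances, admissions, satisfaction or costs.

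**Working it through.** **Inputs.** From Sample size: 1440 patients, so 720 per arm at 1:1; ICC at its bound of 0.02; 50% against 40%; 0.20 SD in SF12. A two-sided 5% level is assumed, as sidedness is not stated. Clusters: 20 paramedics at each of two sites gives 40, with 1440/40 = 36 patients each. The same paragraph also speaks of 20 clusters. That conflict is a separate matter, and the more favourable 40 is used here.

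**Reproducing the stated power.**
- Design effect = 1 + (36 − 1) × 0.02 = 1.70.
- Effective n per arm = 720/1.70 = 423.5.
- Proportions: power = Φ{[|p1 − p2| − 1.96√(2p̄(1 − p̄)/n)] / √([p1(1 − p1) + p2(1 − p2)]/n)}. For 50% against 40% this is Φ{[0.10 − 1.96√(0.495/423.5)] / √(0.49/423.5)} = Φ(0.97) = 83%.
- SF12: Φ{0.20/√(2/423.5) − 1.96} = Φ(0.95) = 83%, if all patients respond.

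The claim of more than 80% is met for both quantities. With 20 clusters it would not be (69% and 68%).

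**Which time point does the 83% belong to?** The protocol does not say. Let T be the period in months to which the 50% and 40% refer. Under a constant hazard the one-month risk is 1 − (1 − p)^(1/T). One-month power at effective n 423.5:

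| Assumed T | One-month risks | One-month power |
|---|---|---|
| 1 month | 50.0% vs 40.0% | 83% |
| 3 months | 20.6% vs 15.7% | 47% |
| 6 months | 10.9% vs 8.2% | 27% |
| 12 months | 5.6% vs 4.2% | 16% |

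If T is six months but events come early, illustrative one-month risks of 20% vs 16% give 33%, and 25% vs 20% give 41%. These two pairs are assumptions, not protocol figures.

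**Number of candidate primary tests.**
- Outcomes: 4 + 4 + 2 + 2 = 12; at two time points, 24.
- Subtract 1 for satisfaction (one month only), 2 for the process times (they belong to the call) and 1 for time to first fall (one analysis): 20.
- Leave out item 4, which is largely estimation (2 outcomes × 2 times = 4): 16.

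Chance of at least one false positive with k independent 5% tests is 1 − 0.95^k: 46% for 12, 56% for 16, 64% for 20. The outcomes are correlated, so these are upper-end illustrations.

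**The case against.** **A statistical analysis plan may name the primary outcome.** It may, and only the protocol is available. But the protocol itself ties its sample size to the primary objective, so it needs to say what that is.

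**The sample size implies the primary outcome.** Further 999 calls for falls is the natural candidate. But SF12 stands beside it on equal terms, neither has a time point, and item 1 lists a count and a time to event instead.

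**SF12 is powered and belongs to item 2.** This stands. SF12 measures quality of life and is collected at both times, with about 83% power at either if all respond. A reader might infer that nothing at one month is powered; that is not so.

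**The horizon is probably six months.** Six-month tracking of contacts makes this plausible, but the protocol does not state it. One-month power therefore cannot be given as a single fact, and the range above is conditional.

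Two further inferences go too far:
- That the count of falls will be diluted. The protocol says that "the impact on outcomes may potentially be diluted by subsequent attendance by a paramedic or ECP using the computerised CDS"; this is a possibility, and it is not tied to the count.
- That falls without a 999 call are known only from questionnaires and cannot be dated. Patients are also tracked through A&E and GPs, and the phrase in item 1 may mean only falls with a 999 call.

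**Conclusion.** The point holds. About twelve outcomes at two time points share the primary label, none is singled out, and the sized proportion is undated and absent from the objective. Some 16 to 20 tests at 5% could each be presented as primary. The statement that the study is powered for processes and outcomes is wider than the two quantities calculated.

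The stated power is arithmetically sound on 40 clusters and an ICC of 0.02, at 83%, but it cannot be assigned to either time point. For horizons of 3, 6 and 12 months, one-month power for further 999 calls would be about 47%, 27% and 16% under a constant hazard; it equals 83% only if the 50% and 40% are themselves one-month figures. A flat statement that the one-month comparison has low power would go beyond the document. The supported conclusion is that its power is unknown until the 50% is dated.

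**What to change.** 1. Name one primary outcome and time point that match the sized quantity: for example, the proportion of patients with at least one further 999 call for a fall within six months of the index call, from ambulance records.
2. Have the investigators state the period to which the London 50% applies. If it is not six months, restate the rates and power in Sample size for the chosen horizon.
3. Define the time-to-event outcome as time to first further 999 call for a fall, from the same records.
4. Label the number of calls, the one-month comparisons and items 2 to 4 as secondary, with SF12 identified as a powered secondary outcome.
5. Limit the power statement in Description of intervention to the two quantities in Sample size.

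No new data are needed, since 999 contacts are already tracked for six months. If the 50% is a six-month figure, the change is one of wording; if not, the power must be recalculated and may prove insufficient. The price is that the investigators give up calling every outcome, including SF12, primary.

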**Study design**

The study is designed as a mixed methods study, utilising a factorial cluster randomised controlled trial (RCT) with a qualitative component

**Description of intervention**

The intervention being evaluated is an IT innovation of CDS software on a hand-held Tablet PC for use on scene by ambulance crews to make decisions about the clinical and social care needs of patients that have called the 999 ambulance service. The innovation is part of a complex intervention with four components: training – both clinical and technology based; decision-support guidance to assess and plan care for older fallers; the hardware and software; and referral to community based care providers. The package will be evaluated as a whole, in line with the recommendations of the MRC for evaluating complex interventions to improve health18, as the component parts are interdependent and should not be separated out for the sole purpose of testing.

The technology will allow the traditional ambulance service Patient Report Form to be replaced with a digital record on the Tablet PC, and trained crews will be expected to use the computer to create an electronic record for every call. When the crew member attends a patient that meets the inclusion criteria for this study, the additional functionality of the decision support for assessing falls will also be used to assess whether the older person who has fallen should be taken to A&E or offered an alternative care plan. The CDS prompts the assessment and examination of any injuries associated with the fall, as well as co-morbidity that may have contributed to the fall (such as breathlessness or chest pain) and the patient’s psycho-social needs (such as their mental state and their ability to undertake activities of daily living). An assessment of environmental risk is also included. Based on these assessments, the CDS suggests an appropriate care plan (such as patient advice, referral to specific community based services etc.).

Paramedics allocated to the intervention group will receive additional training (two days) in the use of the CDS. Following initial training there will be a pre-trial period of one month during which trained crews will be expected to practise using the hand-held computer in place of paper Patient Record Forms, and the CDS for falls assessment as and when appropriate. Towards the end of this period, their use of the CDS will be audited to ensure that they have achieved proficiency. Training will be carried out with groups of 4 paramedics, and will last two days, split so that the initial training is followed up by a refresher training session/competency test after three weeks of practice. Training consists of systematic demonstration of the mechanics and functionality of the software coupled with practice and supervised structured and unstructured role play. Critical reflection and discussion is undertaken and encouraged throughout the training programme. Knowledge reviews are carried out at certain points of the process to ensure competence and understanding of key aspects of the software functionality.

To meet the primary study objective, the technology will be tested with paramedics at two study sites (S Wales, Great Western Ambulance Service). It is intended that crews that have been trained in the intervention will make decisions that can enable community-based care and avoid hospital attendance and admission for these older patients, without undertaking the lengthy, comprehensive and expensive training that is required to enable them to act as fully autonomous practitioners. Building on research findings from previous studies carried out by members of the research team, the technology will form an integral part of the package to be evaluated. Protocols have been shown to have limited impact, but integrated into on-line decision support software to be used interactively on scene, may allow identification of patients who can be safely left at home. Thus patients may benefit from a more appropriate response in their homes rather than the traditional care of transportation to A&E, or non-conveyance without referral - because they have been left at home outside protocols. The study will be powered to detect differences in processes and outcomes between patients in the intervention and control groups in these two sites.

**Sample information on size, type, location and whether the sample will be representative or not**

The study will take place in two ambulance service sites who have expressed enthusiasm concerning participation in this timely trial - South Wales and Great Western. Paramedics eligible for inclusion in the study will be randomly selected to the intervention or control groups. In the two sites, half of the recruited paramedics based at the ambulance stations in the catchment area of 1 District General Hospital with a full A&E department service will be trained to use the CDS algorithms and the hand-held device for face-to-face consultation. All older patients that have had falls and are attended by crews during the data collection period will be included in the sample. Randomisation and recruitment to the trial will be facilitated and monitored through WORTH (Wales Organisation for Randomised Trials in Health). Those not attended by an intervention group paramedic will receive the standard treatment. As it will not be practical to blind the dispatchers in ambulance control to the study group of paramedics, it will be necessary to monitor and potentially manage ambulance dispatch to avoid any selection bias, which might manifest itself in a higher pick-up or recruitment rate in the intervention group. Paramedics allocated to the intervention group will receive additional training (four days) and the hardware, as well as protocols and telephone/fax numbers for referral.

*Inclusion criteria:* 999 call for patient aged over 65 attended by a study paramedic and classified by them as having fallen. In order to maximise generalisability of findings to this group of frail patients with complex needs no patients will be excluded due to other conditions or competence. Where necessary, outcomes will be followed up with carers.

*Sample size*: The sample size for the two paramedic sites (S Wales and Great Western) is calculated for the primary objective, and with 20 paramedics (ten in each intervention group, 10 in each control group) at each site. Based on ambulance service data from the participating services, it is expected to recruit 250 older people who have fallen in each site each month. However, it may not be possible to identify all those who have fallen as eligible for inclusion in the study from information given during the 999 call, and some patients will not consent to be included. Using a conservative estimate of the recruitment of 80 older people who have fallen attended by study paramedics per month, a period of nine months will allow inclusion of 720 patients per site (1440 in total). With the 20 clusters, this will give more than 80% power at the 5% significance level to detect a drop in further 999 calls for falls from 50% (as found in London recently6) to 40%, assuming an intra-class correlation of less than 0.02, and to detect an effect size of 0.20 (i.e. one fifth of the population standard deviation) in SF12 scores.

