*Outcomes:* Patients will be tracked through the 999 system, A&E departments, GPs and coroners to identify further contacts with these services (or death) following a fall within six months. Referrals will be followed up and contacts with other service providers recorded. Quality of life of patients and carers, self-reported falls and independence will be followed up by questionnaire, to be administered by post (or interview, where necessary), including the SF1220 , EQ5D21 and the CGI22 at 1 and 6 months; patient satisfaction will also be followed up at 1 month with the Quality of Care Monitor23. Despite using several validated outcome measures, care has been taken to select brief tools and efforts will be made to keep the questionnaire as short as possible in order to minimise the burden on respondents and to maximise response rate. Job cycle times will be recorded for all calls meeting the study inclusion criteria, from routine ambulance records.

*Health economics:* The economic analysis will estimate the costs of providing the new intervention, the consequences of the scheme for the wider NHS (eg A&E attendances, inpatient admissions) and the costs to patients and families. Data on the use of the health service resources will be collected for each patient using a combination of paramedic records, routine hospital records (for hospital events) and patient-completed questionnaires. Costs will then be calculated using unit-costs estimated through a micro-costing study within the trial. Direct costs to the NHS will be assessed using data logged as a part of routine practice and from resource utilisation recording sheets, together with reference to patient records and discussions with relevant finance staff. The EQ5D will also be used to estimate the quality adjusted life years (QALYs) gained from the intervention and an incremental cost-per-QALY estimated. These ratios will be presented along with their associated cost-effectiveness acceptability curves. Sensitivity analysis will be undertaken to assess the robustness of the results to changes in the configuration of the scheme and other health service costs.

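### The SF12 power statement counts all 1440 included patients, with no allowance for unreturned questionnaires or deaths; at the ICC bound of 0.02 it needs about 88% scored returns

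*Protocol*

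**What the plan says.** The Sample size paragraph (Protocol, 'Sample information on size, type, location and whether the sample will be representative or not') starts from 250 older fallers per site per month. It reduces this to 80 because some will not be identified from the call and some will not consent. From there, "a period of nine months will allow inclusion of 720 patients per site (1440 in total"). It then says that "this will give more than 80% power at the 5% significance level" for two outcomes: a drop in further 999 calls for falls from 50% to 40%, "assuming an intra-class correlation of less than 0.02", and, in the same sentence, "to detect an effect size of 0.20 (i.e. one fifth of the population standard deviation) in SF12 scores". No separate number of patients and no separate ICC is given for SF12.

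The two outcomes are collected differently. Under 'Methods to be used', Outcomes, patients are tracked through the 999 system and other services. For SF12, "Quality of life of patients and carers, self-reported falls and independence will be followed up by questionnaire, to be administered by post", with interview where necessary, at 1 and 6 months. The same paragraph aims for a short form to help response, but states no expected response rate. Under Consent, patients reply only if they wish to opt out. The inclusion criteria describe a frail group, exclude nobody for other conditions or competence, and allow follow-up through carers where necessary.

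**The concern.** Inclusion and response are different things here. Under opt-out, a patient who never answers any post stays among the 1440 and contributes 999-call data, but no SF12 score. A patient who dies before 1 or 6 months also remains included and cannot provide SF12 afterwards. The cut from 250 to 80 per month is explained by non-identification and non-consent, so it does not cover either loss.

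Quality of life is listed under the primary objective, and SF12 is one of only two outcomes with a stated detectable effect. If the number of scored forms falls short, a null SF12 result could be read against a power that the trial did not have. This is not a detail left for an analysis plan, because the protocol itself states the power figure.

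**Working it through.** **Inputs from the protocol.**
- Patients: 1440, taken as 720 per arm, since "half of the recruited paramedics based at the ambulance stations" in the catchment are trained.
- Effect: 0.20 SD. Significance level: 5%, taken as two-sided (the protocol does not say).
- ICC: 0.02, the upper bound of what is assumed.
- Clusters: the paramedic is the unit, "with 20 paramedics (ten in each intervention group, 10 in each control group) at each site", so 2 × 20 = 40 in total, 20 per arm.

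**Assumption not in the protocol.** The proportion r of included patients with a scored SF12 at the analysed time point, shown as a range.

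**Formulas.**
- Scored patients n = 1440r; mean cluster size m = n/40 = 36r
- Design effect DE = 1 + (m − 1) × ICC
- Effective number per arm = 720r/DE
- Power = Φ(0.20 × √(effective n/2) − 1.96)
- Effect detectable at 80% power = 2.802 × √(2/effective n), in SD units
- The t version uses the non-central t distribution on 40 − 2 = 38 df with the same non-centrality.

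**Step 1: the protocol's own figure (r = 1).** m = 36; DE = 1 + 35 × 0.02 = 1.70; effective n = 720/1.70 = 423.5 per arm. Power = Φ(0.20 × √211.8 − 1.96) = Φ(0.95) = 82.9%, or 81.0% with t. The stated figure of more than 80% is reproduced, with every included patient scored.

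**Step 2: power when fewer are scored (40 clusters, ICC 0.02).**

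| Scored return (assumed) | n | m | DE | Effective n per arm | Power | Power (t, 38 df) | Detectable at 80% power |
|---|---|---|---|---|---|---|---|
| 100% | 1440 | 36.0 | 1.700 | 423.5 | 82.9% | 81.0% | 0.193 SD |
| 90% | 1296 | 32.4 | 1.628 | 398.0 | 80.6% | 78.5% | 0.199 SD |
| 80% | 1152 | 28.8 | 1.556 | 370.2 | 77.7% | 75.5% | 0.206 SD |
| 70% | 1008 | 25.2 | 1.484 | 339.6 | 74.1% | 71.9% | 0.215 SD |
| 60% | 864 | 21.6 | 1.412 | 305.9 | 69.6% | 67.4% | 0.227 SD |
| 50% | 720 | 18.0 | 1.340 | 268.7 | 64.0% | 61.8% | 0.242 SD |

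The last column uses the normal approximation.

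**Step 3: return needed for 80% power.** About 393 effective patients per arm are required.

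| ICC | Return needed | Return needed (t, 38 df) |
|---|---|---|
| 0.02 | 88.0% (1267 patients) | 95.9% (1381) |
| 0.015 | 76.1% (1096) | 82.0% (1181) |
| 0.01 | 67.2% (968) | 71.7% (1032) |
| 0.005 | 60.2% (867) | 63.7% (917) |
| 0 | 54.6% (786) | 57.4% (827) |

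A smaller ICC therefore helps a good deal, but not without limit: at 50% return, power is 76.5% even with no clustering at all.

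**The case against.** The strongest reply is that the stated figure reproduces, so there is no slip in the arithmetic, and that it has some slack. Under the normal approximation the trial can lose about 12% of forms (1440 − 1267 = 173) at an ICC of 0.02 and still have 80% power. The protocol assumes an ICC below 0.02, not equal to it, and at 0.01 a return of about two thirds is enough. Interviews and carer follow-up are planned. The recruitment rate is called conservative: at 70% return, 1267 scored forms would need 1267/0.70 = 1810 inclusions, or 1810/18 site-months ≈ 101 per site per month, against 250 expected fallers.

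Most of this stands as a limit on how far the point goes. It does not remove it. A power claim made for any ICC below 0.02 should hold close to that bound. The recruitment margin is not set aside for non-return. Interview and carer follow-up are not quantified, and neither can supply a score for a patient who has died.

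A reader might infer three stronger conclusions, which the protocol does not support:
- **That the claim requires all 1440 forms, or that postal follow-up cannot deliver enough.** The threshold at ICC 0.02 is about 88%, or 96% with t. No response rate is given, so complete return is implausible in this group but a return below the threshold is not shown.
- **That power is misstated for every self-reported outcome.** It is stated for SF12 only.
- **That the reference to 20 clusters makes this worse.** If 20 meant the total, power would be 68.4% even at full return. That question affects the 999-call outcome as well, has nothing to do with non-response, and is a separate point.

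**Conclusion.** The point holds as an omitted allowance in a stated design property. The SF12 power is supported only at near-complete scored return when the ICC is at the protocol's bound: 82.9% at full return, and below 80% once fewer than about 88% are scored (96% with t on 38 df). Over assumed returns of 80% to 50%, power for 0.20 SD falls from about 78% to 64%, and the effect detectable at 80% power rises from 0.206 to 0.242 SD.

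These figures rest on 40 paramedic clusters of equal size, 1:1 allocation, a two-sided 5% test and an ICC of 0.02 carried over to SF12. The return rates are assumptions. With a lower ICC the claim could hold at a moderate return, so the true shortfall may be small or absent, and the protocol does not allow a reader to tell. The 999-call power does not depend on questionnaire return.

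**What to change.** State the SF12 power in its own sentence, apart from the 999-call outcome. Base it on the expected number of scored questionnaires at the time point to be analysed (1 or 6 months), and give the assumed return, including the allowance for deaths, and the assumed ICC. For example: with 60 to 70% scored return (864 to 1008 patients), 40 clusters and an ICC of 0.02, the trial has 80% power for an SF12 difference of 0.215 to 0.227 SD, and 70 to 74% power for 0.20 SD. If the team expects a lower ICC or a higher return, it should give that value and its basis.

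The cost is one sentence and a slightly less favourable stated figure. No extra patients are needed, and the 999-call calculation need not change on this account.
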